## Abstract

**Introduction:**

Profiles of high risk for future dementia are well understood and are likely to concern mostly those in low-income and middle-income countries and people at greater disadvantage in high-income countries. Approximately 30%–40% of dementia cases have been estimated to be attributed to modifiable risk factors, including hypertension, smoking and sedentary lifestyle. Tailored interventions targeting these risk factors can potentially prevent or delay the onset of dementia. Mobile health (mHealth) improves accessibility of such prevention strategies in hard-to-reach populations while at the same time tailoring such approaches. In the current study, we will investigate the effectiveness and implementation of a coach-supported mHealth intervention, targeting dementia risk factors, to reduce dementia risk.

**Methods and analysis:**

The prevention of dementia using mobile phone applications (PRODEMOS) randomised controlled trial will follow an effectiveness–implementation hybrid design, taking place in the UK and China. People are eligible if they are 55–75 years old, of low socioeconomic status (UK) or from the general population (China); have ≥2 dementia risk factors; and own a smartphone. 2400 participants will be randomised to either a coach-supported, interactive mHealth platform, facilitating self-management of dementia risk factors, or a static control platform. The intervention and follow-up period will be 18 months. The primary effectiveness outcome is change in the previously validated Cardiovascular Risk Factors, Ageing and Incidence of Dementia dementia risk score. The main secondary outcomes include improvement of individual risk factors and cost-effectiveness. Implementation outcomes include acceptability, adoption, feasibility and sustainability of the intervention.

**Ethics and dissemination:**

The PRODEMOS trial is sponsored in the UK by the University of Cambridge and is granted ethical approval by the London—Brighton and Sussex Research Ethics Committee (reference: 20/LO/01440). In China, the trial is approved by the medical ethics committees of Capital Medical University, Beijing Tiantan Hospital, Beijing Geriatric Hospital, Chinese People’s Liberation Army General Hospital, Taishan Medical University and Xuanwu Hospital. Results will be published in a peer-reviewed journal.

**Trial registration number:**

ISRCTN15986016.

Strengths and limitations of this studyThe coach-supported mobile health intervention builds on the previously developed Healthy Ageing Through Internet Counselling in the Elderly electronic health platform, which was shown to improve cardiovascular risk of elderly in the Netherlands, France and Finland.The main strengths of the present study are testing the approach in populations with low socioeconomic status or different cultural settings and measuring whether sustained involvement of end users can be achieved, facilitating cultural adaptation of the application.Limitations of this study include the impossibility to completely blinding the participants, potentially leading to contamination, and the challenge to sufficiently engage the hard-to-reach target population.

## Introduction

With global ageing, the prevalence of dementia is expected to increase to over 130 million in 2050, especially in low-income and middle-income countries (LMIC) and in people from low socioeconomic status (SES) background in high-income countries (HIC).^1 2^ Strategies need to be developed that aim to reduce the risk of dementia—many of which will be at community and population level, but those that are individually based must be effective, affordable and easily implementable across various healthcare settings.

Up to 40% of dementia cases are estimated to be attributable to potentially modifiable risk factors,^3^ of which 10%–20% are cardiovascular risk factors including hypertension, midlife obesity, dyslipidaemia, diabetes, smoking and physical inactivity.^4–6^ To date, intervention studies aiming to reduce dementia risk by targeting one or more of these risk factors have shown inconsistent results.^7 8^ Results from randomised controlled trials (RCT) on blood pressure-lowering treatment have suggested a beneficial effect on dementia risk, although not consistently and convincingly.^9–11^ Since the presence of multiple risk factors may pose an additive or even synergistic effect on dementia risk,^12 13^ targeting several risk factors simultaneously may be more effective. The only study to date designed to address this question using dementia as primary outcome did not show a statistically significant effect after 6–8 years of intervention, although subgroup analysis suggested benefit for those with untreated hypertension at baseline.^14^

A considerable challenge when designing a dementia prevention trial is the time lag between the optimal timing of the intervention and the onset of dementia. Using incident dementia as primary outcome requires large sample sizes and/or long follow-up periods to reach statistical power.^15 16^ Dementia risk scores could be used as a proxy, especially in trials with follow-up periods up to several years. Another challenge, possibly explaining the neutral results of intervention studies so far, is the small window for risk factor improvement given a background of high-quality cardiovascular risk management in HIC where these studies were performed.^17^ This lends further support for targeting people in LMIC and low-SES populations in HIC.

Digital health interventions have the potential to improve cardiovascular risk factors in middle age and beyond, especially when offered with human coaching (blended care).^18^ In the Healthy Ageing Through Internet Counselling in the Elderly (HATICE) trial, we recently demonstrated that a coach-supported internet intervention facilitating self-management of cardiovascular risk factors can reduce older adults’ cardiovascular risk over a static control platform, both in high and low socioeconomic participant subgroups.^19^ Currently, digital health interventions are increasingly offered through smartphones. Smartphone penetration rates are especially high in HIC,^20^ also among people with low SES. In 2018, 67% of people with the lowest SES in UK owned a smartphone.^21^ Approximately 40%–50% of the LMIC population is connected to mobile internet,^20 22^ with rates up to 60% in China.^23^ This renders mobile health (mHealth) a promising method for health delivery in underserved populations, including the improvement of cardiovascular risk factors.^24 25^

We have developed a coach-supported mHealth intervention to reduce dementia risk by addressing common cardiovascular risk factors via lifestyle changes, building on the existing HATICE internet platform. Our aim is to assess the effectiveness and implementation of this smartphone intervention on dementia risk in older people at increased risk of dementia from a low-SES population in the UK and from the general population in Beijing, China.

## Methods

### Study design

Prevention of dementia using mobile phone applications (PRODEMOS) is a multinational, prospective, randomised, open-label blinded endpoint trial with 18-month intervention and follow-up. The study follows a hybrid effectiveness–implementation design, taking a dual focus on assessing effectiveness and implementation outcomes.^26 27^ The Amsterdam University Medical Centre (Amsterdam UMC) is the coordinating centre.

### Study population and recruitment

The study population will consist of community-dwelling older adults aged 55–75 years old, of low SES in the UK and of any SES in China, who have ≥2 dementia risk factors and own a smartphone. Low SES in the UK is operationalised as living in a postal code area ranked as equal to or less than the lowest third decile of the index of multiple deprivation.^28^ Eligibility criteria are similar for both countries, except for criteria for obesity, based on differences in national prevention guidelines^29^ (box 1).

Box 1Overview of inclusion and exclusion criteriaInclusion criteriaAge ≥55 years and ≤75 years old.Living in a postal code area ranked as equal to or less than the lowest third decile of IMD*.Good proficiency of the national language (English in UK and Mandarin in China).Possession of a smartphone.≥ Two dementia risk factors:Insufficient physical activity (self-reported intermediate or vigorous activity of <150 min per week).Active smoking (self-reported use of any sort of tobacco in any quantity).Depression (by meeting at least one of the following criteria):Current diagnosis by specialist or GP.History of treatment for depression (ie, drug therapy or psychotherapy).Manifest cardiovascular disease, as diagnosed by specialist or GP.Diabetes mellitus (by meeting at least one of the following criteria):Diagnosed by specialist or GP.Use of insulin or other blood glucose-lowering medication.Hypertension (by meeting at least one of the following criteria):Diagnosed by specialist or GP.Use of blood pressure-lowering medication.Mean of baseline blood pressure measurements of ≥140 (systolic) or ≥90 (diastolic).Obesity (by meeting at least one of the following criteria):BMI ≥30 (UK) and ≥28 (China).Baseline waist circumference ≥102 cm (men in UK), 90 cm (men in China), 88 cm (women in UK) and 85 cm (women in China).Dyslipidaemia (by meeting at least one of the following criteria):Diagnosed by specialist or GP.Use of lipid-lowering medication.Baseline total cholesterol ≥5.0 mmol/L*.Exclusion criteriaManifest dementia, as diagnosed by specialist or GP.MMSE <24 (participants with ISCED level of >1) and MMSE <21 (participants with ISCED level of 1).Any condition expected to limit 18-month follow-up, including metastasised malignancy or other terminal illnesses.Smartphone illiteracy, defined as not being able to send a message from a smartphone.Visual impairment interfering with operation of a smartphone.Participating in another RCT on behaviour change.Present severe alcohol or illicit drug abuse.* Applies only to participants in the UKBMI, Body Mass Index; GP, general practitioner; IMD, Index of Multiple Deprivation; ISCED, International Standard Classification of Education; MMSE, Mini-Mental State Examination; RCT, randomised controlled trial.

Recruitment will take place in the Eastern Clinical Research Network (National Institutes of Health Research) region of the UK and in the Beijing and Tai’an cities, China. In the UK, recruitment has started in January 2021 and will be undertaken by approximately 10–15 general practioner (GP) practice. A random computer selection of participants living in the designated postal code areas meeting the age criterion and having ≥1 known dementia risk factor according to the GP registry will be approached through an information letter, inviting them to contact the local study centre. In China, participants will be recruited from seven hospitals through advertisements on hospital websites, targeted recruitment via local social media (WeChat) or direct approach by nurses and physicians. In China, recruitment is expected to start mid-2021.

### Intervention and control condition

Central to our study is the PRODEMOS platform, which interconnects the assessor portal, the participant app and the coach portal (figure 1). The assessor portal facilitates blinded collection of baseline and outcome assessments for all participants. The intervention and control condition are both delivered through a smartphone app, which, in the case of intervention participants, allows communication with the coach portal. Data from the assessor portal, participant app and coach portal can be extracted through a researcher portal and stored in a central database. The PRODEMOS platform was built in close collaboration between software developers and researchers from Amsterdam UMC, University of Cambridge, Brighton and Sussex Medical School, Capital Medical University in Beijing, health coaches and representatives of the target population from both countries. The internet platform previously used in the HATICE trial served as the basis for the PRODEMOS platform.^30^ In addition to the transition of the participants’ end into a mobile app, adjustments were made to the platform in repeated cycles of interaction with end users. In an iterative process, experiences, needs and wishes from the target population and health coaches regarding the app and coach support, gained through interviews and focus groups, served as a guideline for further development.

**Figure 1 F1:**
[figure not shown]
Overview of the prevention of dementia using mobile phone applications (PRODEMOS) platform and its functionalities. Main features of coach portal: viewing and adjusting details of goals and measurements; sending and receiving chat messages to and from the participants; sending education and news items. Main features of intervention app: setting and adjusting goals; entering measurements; sending and receiving chat messages to and from the coach; reading education and news items automatically pushed by platform or received from the coach; receiving periodic adverse event questionnaires and self-assessment questionnaires. Main features of assessor portal: blinded collection of participant data through electronic case report forms and questionnaires. The control application has similar connections with the assessor portal and the researcher portal/database, but is not connected to the coach portal.

Participants have only access to one of two versions of the participant app. Participants randomised to the intervention condition will have access to an interactive smartphone application in their own language (English in the UK and Mandarin in China). The intervention app facilitates coach-supported self-management of seven dementia risk factors, including overweight, unhealthy diet, insufficient physical activity, smoking, hypertension, dyslipidaemia and diabetes. Participants can set personal goals for lifestyle change, following the specific, measurable, achievable, realistic and time-bound principle. Participants receive automated reminders to enter measurements (eg, number of steps and blood pressure) for these goals, facilitating progress monitoring. The intervention participants will receive support from an experienced lifestyle coach, who is trained in motivational interviewing and works according to a coach protocol based on current guidelines for risk factor management. Regular training sessions in each country will enhance uniformity in coaching procedures, taking cultural differences into account. During the baseline visit, after randomisation, the coach discusses the participant’s dementia risk profile, and a first lifestyle goal will be set through the app. After the baseline visit, all communication between the participant and coach will take place through the messaging functionality. Through the coach portal, the coach can view goals and measurements, send tailored education modules, and offer remote support to facilitate sustainable behaviour change.

Participants randomised to the control condition will have access to the control app, which is similar in appearance but only contains education material, lacking interactive features and coach-support. During the baseline visit, control participants will receive concise feedback on their risk profile.

The PRODEMOS intervention in its current design is positioned as add-on to existing care.

### Primary and secondary outcomes

Following a type II hybrid design, primary outcomes for effectiveness and implementation are equally important. The primary effectiveness outcome is the change in the Cardiovascular Risk Factors, Ageing and Incidence of Dementia (CAIDE) dementia risk score between baseline and 18-month follow-up.^31^ The main secondary effectiveness outcomes include change in the individual modifiable components of the primary outcome, change in ten-year cardiovascular disease (CVD) risk, cost-effectiveness and certain clinical outcomes such as incidence of mild cognitive impairment (MCI) and dementia. The operationalisation of all effectiveness outcomes is listed in table 1.

**Table 1 T1:** Effectiveness outcomes

Primary outcome	Points
CAIDE Score (range: 0–15), which is composed of and calculated from the following:	
Age	
<47 years	0
47–53	3
>53	4
Education	
≥10 years	0
7–9 years	2
<7 years	3
Gender	
Female	0
Male	1
Systolic blood pressure	
≤140 mm Hg	0
>140 mm Hg	2
BMI	
≤30 kg/m^2^	0
>30 kg/m^2^	2
Total cholesterol	
≤6.5 mmol/L	0
>6.5 mmol/L	2
Physical activity*	
Yes	0
No	1
**Secondary outcomes**	
Individual modifiable components of the CAIDE score†	Estimated 10-year cardiovascular risk
Number of uncontrolled risk factors	LIBRA dementia risk score
Active smoking	Number of hospital admissions
Medication adherence	Diet‡
Number of drugs	Disability§
Incident dementia¶	Anxiety**
Incident MCI¶	Self-management††
Incident cardiovascular disease¶,§§	Depressive symptoms‡‡
Incident diabetes¶	Quality of life¶¶
All-cause mortality	Cost-effectiveness

*Assessed according to WHO standard for physical activity of at least 150 min per week.

†Physical activity assessed with the International Physical Activity Questionnaire—Short Form.

‡Assessed with Short-Form Food Frequency Questionnaire (UK) and China Kadoorie Biobank Food Frequency Questionnaire (China).

§Assessed with the WHO Disability Assessment Schedule.

¶Self-reported and cross-checked with general practitioner file.

**Assessed with the Hospital Anxiety and Depression Scale—Anxiety.

††Assessed with the Partners In Health.

‡‡Assessed with the Geriatric Depression Scale.

§§Defined as myocardial infarction or stroke.

¶¶Assessed with the ICEpop CAPability Measure for Adults and EuroQol Five Dimensions Three Levels.

BMI, Body Mass Index; CAIDE, Cardiovascular Risk Factors, Ageing and Incidence of Dementia; LIBRA, Lifestyle for Brain Health; MCI, mild cognitive impairment.

Implementation outcomes include acceptability, adoption, appropriateness, feasibility, fidelity, coverage, sustainability and costs of the implementation. User statistics, including data on goals set, messages sent and education items read, will be analysed to assess adoption and sustained use of the platform. In-depth interviews with participants and coaches will focus on user experiences, particularly with respect to barriers and facilitators for (sustained) platform use. All implementation outcomes and evaluation methods are shown in table 2.

**Table 2 T2:** Summary of implementation research methods and outcomes

Method	Outcome	Measurement	Population*	Timing of assessment
Quantitative	Coverage	(Non)Response rates, comparison characteristics of participants with eligible population	Potential target population	At baseline
	Adoption	Utilisation, usage, and uptake	Intervention participants, coaches	After 2 weeks
	Appropriateness	Short questionnaire of perceived fit or relevance in the target population and the coaches	Intervention participants, coaches	After 3 months and at study end
	Acceptability	Short questionnaire of agreeability, user-friendliness, credibility	Intervention participants, coaches	After 3 months and at study end
	Sustainability	Adherence, dropout	Intervention participants, dropouts†	Throughout the study
	Cost	Implementation costs	N.A.	N.A.
Qualitative	Feasibility	The extent to which the mHealth intervention can be carried out →practical and social barriers/facilitators	Intervention participants, dropouts,† coaches	After 3 months and at study end
	Appropriateness	Perceived fit or relevance in the target population	Intervention participants, dropouts,† coaches	After 3 months and at study end
	Acceptability	Agreeability, user-friendliness, credibility	Intervention participants, dropouts,† coaches	After 3 months and at study end
	Fidelity	Degree to which the mHealth application is implemented compared with the original protocol	N.A.	After the study

*For all analyses, a Chinese and UK population will be involved.

†Study dropouts will be asked to participate in a short exit interview.

mHealth, mobile health.

### Study logistics and data collection

The trial design is visualised in figure 2. All participants will receive one phone call and make three visits to a study venue during the study. Data are collected in electronic case report forms that are accessible through the assessor portal (figure 1).

**Figure 2 F2:**
[figure not shown]
Trial design. AE, adverse event; ISCED, International Standard Classification of Education; MMSE, Mini-Mental State Examination; RCT, randomised controlled trial.

Eligibility criteria that can be assessed remotely will be checked by a local research team member through the screening phone call. During the subsequent screening visit, informed consent (online supplemental file 1) will be obtained, and final eligibility will be assessed by administering the Mini-Mental State Examination; measuring blood pressure, Body Mass Index, waist circumference and total cholesterol (capillary blood sample in the UK; venous blood sample in China); and assessing physical activity, smoking behaviour and a brief medical history. Weight will be measured with a calibrated scale; blood pressure will be measured twice with a calibrated, automated blood pressure device. Screening visits will be performed by (GP) nurses and local research team members specifically trained to perform these measurements and will take place at the GP surgery or a nearby community venue. Standard operating procedures will be used to achieve uniform measurements within and between countries.

10.1136/bmjopen-2021-049762.supp1Supplementary data

After the screening visit, all participants will fill in eight self-assessment questionnaires in the PRODEMOS app. These questionnaires will be used to assess secondary outcomes (ie, physical activity, quality of life, well-being, disability, depressive symptoms, self-management, anxiety and diet; table 1) and potential barriers for lifestyle behaviour change, which can inform coaches to tailor their coaching strategy. Seven of these questionnaires (ie, International Physical Activity Questionnaire—Short Form, EuroQol Five Dimensions, ICEpop CAPability Measure for Adults, WHO Disability Assessment Schedule 2.0, Geriatric Depression Scale (GDS), Partners In Health and Hospital Anxiety and Depression Scale–Anxiety) have been externally validated in both Western and Chinese populations.^32–45^ Owing to obvious cultural differences, we decided to use two different diet questionnaires that were validated in the UK and Chinese population, respectively (Short-Form Food Frequency Questionnaire and Kadoorie Biobank Food Frequency Questionnaire).^46 47^

The baseline visit will be conducted face-to-face by the health coach at the GP practice or local community venue. During this visit, self-assessment questionnaires are reviewed, relevant medical history and medication use are recorded, and participants are randomly assigned to one of the treatment conditions. Only intervention participants will set a first lifestyle goal together with the coach, according to their dementia risk profile.

All participants will receive periodic adverse event (AE) questionnaires in the app, assessing incident dementia, MCI, CVD and diabetes. All self-reported outcomes will be verified with the participant’s treating physician.

After 18 months, the questionnaires and all measurements performed during the screening and baseline visit are repeated during the final visit.

### Randomisation and blinding

After completion of the baseline assessments, participants will be individually randomised in a 1:1 ratio, stratified by country, using a central, computer-generated sequence. Participating cohabiting partners will be allocated to the same study condition. Complete blinding of participants is not possible, owing to the nature of the intervention. Participants will be informed that they will be randomised to one of two lifestyle apps, without further details. All outcome assessments will be done by an independent assessor unaware of treatment allocation.

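### The blinded-endpoint claim is too broad: the physical-activity item of the primary CAIDE score appears to be participant-reported, and only the intervention arm is coached on activity

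*Protocol article*

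**What the plan says.** Under Study design, the protocol article calls the trial a "randomised, open-label blinded endpoint trial with 18-month intervention and follow-up". Randomisation and blinding adds, for every outcome: "All outcome assessments will be done by an independent assessor unaware of treatment allocation". The same section concedes: "Complete blinding of participants is not possible, owing to the nature of the intervention".

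The primary endpoint is given under Primary and secondary outcomes: "The primary effectiveness outcome is the change in the Cardiovascular Risk Factors, Ageing and Incidence of Dementia (CAIDE) dementia risk score", between baseline and 18 months. Table 1 gives the activity item 0 points for yes and 1 for no. Its footnote reads "Assessed according to WHO standard for physical activity of at least 150 min per week" and names no instrument.

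Activity is described as a source of data in two other places. Box 1 has the eligibility factor "Insufficient physical activity (self-reported intermediate or vigorous activity of <150 min per week". The Table 1 footnote on the individual CAIDE components says "Physical activity assessed with the International Physical Activity Questionnaire—Short Form", and Study logistics and data collection lists this questionnaire among the self-assessments completed in the app. That section also has staff assess activity at the screening visit, without saying how, and repeats all questionnaires and measurements at the final visit.

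Under Intervention and control condition, insufficient physical activity is one of seven coached risk factors. Goal setting, reminders to enter measurements such as steps, and coach contact belong to the intervention app only.

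**The concern.** For a self-reported item the respondent supplies the measurement. An assessor who is unaware of allocation can record the answer neutrally, but cannot remove what the participant knows. A coached participant has had goals, reminders and messages for up to 18 months, and may be readier than a control to report reaching the 150-minute mark.

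This error would favour the intervention. The Limitations section concedes partial blinding, but the consequences it discusses (contamination, disclosure of baseline results, Hawthorne effects in both arms) would dilute or mask the contrast. It does not mention reporting bias in the opposite direction.

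The size of the target makes this matter. The trial is planned around a difference of 0.186 points, and one person wrongly crossing the activity cut-point moves that person's score by a full point.

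**Working it through.** **Inputs** (Sample size section unless stated): target difference 0.186; SDs of change 1.47 and 1.36; 80% power; two-sided 0.05; 21% attrition; 2400 randomised. Allocation is 1:1 (Randomisation and blinding). The activity item is worth 1 point (Table 1).

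**Step 1: reproduce the plan's sample size.**
- Pooled SD = √[(1.47² + 1.36²)/2] = 1.416.
- n per arm = 2 × (1.960 + 0.842)² × 1.416² / 0.186² = 910, so 1820 in total.
- With attrition: 1820 / 0.79 = 2304 (2306 with the t distribution). The protocol states 2319, which is within 1%, so the inputs are read correctly.

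**Step 2: precision at the planned size.**
- Completers per arm = 2400 × 0.79 / 2 = 948.
- SE = 1.416 × √(2/948) = 0.0650.
- Smallest observed difference with p<0.05 = 1.96 × 0.0650 = 0.1275 points.

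**Step 3: effect of differential reporting.** Baseline activity is recorded before randomisation, so its error is balanced in expectation; only the 18-month report can differ by arm. If the share wrongly reported as active is x higher in the intervention arm than in the control arm, the mean CAIDE difference shifts by x × 1 point. With no true effect, and with b for that shift, the two-sided rejection probability is Φ(b/SE − 1.96) + Φ(−b/SE − 1.96).

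| Net differential over-reporting (percentage points) | Shift b | Share of 0.186 | b/SE | Chance of p<0.05 |
|---|---|---|---|---|
| 0 | 0 | 0% | 0 | 5% |
| 5 | 0.05 | 27% | 0.77 | 12% |
| 10 | 0.10 | 54% | 1.54 | 34% |
| 12.7 | 0.1275 | 69% | 1.96 | 50% |
| 18.6 | 0.186 | 100% | 2.86 | 82% |

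**Step 4: how much misreporting this means.** Only inactive people can over-report. The article does not give the share inactive at 18 months. Assuming 40% to 80%, the 12.7-point case needs 0.1275/0.40 = 32% down to 0.1275/0.80 = 16% of inactive intervention participants to over-report, beyond whatever controls do. Matching 0.186 needs 47% down to 23%.

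**Step 5: sensitivity.** With an SD of 1.2 or 1.6 the significance limit becomes 10.8 or 14.4 percentage points. With 2319 randomised it is 13.0; with no attrition among 2400 it is 11.3. The calculation is a simple two-arm comparison of mean change. It ignores clustering in partner pairs and any small change in SD caused by misreporting.

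**The case against.** **The assessor sentence is literally about the assessor.** It stands beside an admission that participants cannot be fully blinded, and the design is called open-label. That is fair, and the sentence need not be false as a description of staff. Even so, the blinded-endpoint label together with a statement covering all outcomes tells a reader that the primary score is protected, and for this item it is not.

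**The self-report premise is inferred.** The word self-reported belongs to the eligibility criterion, the questionnaire footnote belongs to the secondary component analysis, and the CAIDE item names no instrument. This stands as a qualification. But no objective activity outcome is described anywhere, and either described source leads to the same conclusion. The statement that self-reported outcomes are checked with the treating physician follows the adverse-event questionnaires on dementia, MCI, CVD and diabetes. Nothing suggests that it covers weekly activity minutes.

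**Blinding is partial, not absent.** Participants are told only that they will receive one of two lifestyle apps. Controls get a similar-looking app, education material and risk feedback, so they too learn what is desirable. This is right, and it is why only the net difference between arms counts.

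**The item is small and the components are analysed anyway.** Activity carries 1 point, against 6 for blood pressure, BMI and cholesterol together. The planned component models would show if activity alone moved. That helps a reader, but it does not give the CAIDE-scale effect without the item.

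**Stronger readings.** A reader might infer that about 13 points of over-reporting produces a significant result. It puts the expected difference on the threshold, which is an even chance, and Step 4 shows that this is not a trivial amount of misreporting. A reader might also infer that the trial has no analysis addressing this. The Data analysis section lists none, but it refers to a full analysis plan published elsewhere and not shown here, so absence cannot be claimed.

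**Conclusion.** The point holds as a defect in the blinding claim and in the stated limitations. The Study design and Randomisation and blinding sections extend blinded assessment to a 1-point item of the primary score that appears to rest on the report of participants who are not fully blinded and who are coached on that behaviour in one arm only.

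The possible consequence is material against a 0.186-point target: a net differential of 5 percentage points would more than double the nominal 5% error rate, and 10 points would bring it to about one in three. This rests on three assumptions: that the CAIDE item is scored from self-report, that there is no true effect, and that the SD and attrition match the planning values. The amount of over-reporting is unknown, so the figures show sensitivity and do not predict bias. The measured items are not affected.

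**What to change.** 1. In Study design and in Randomisation and blinding, limit the blinded-assessment claim to the measured CAIDE items (systolic blood pressure, BMI, total cholesterol). State that the activity item is participant-reported, and name its instrument.
2. In Limitations, add that over-reporting in the coached arm could bias the primary result in favour of the intervention.
3. Unless the full analysis plan already has it, pre-specify a supporting analysis: the same linear mixed model, fitted to change in CAIDE computed without the activity item. Report the estimate and its confidence interval next to the primary result, with no pass/fail rule on how much of the effect must remain. Activity is a genuine target of the intervention, so a real gain would also shrink the reduced-score estimate.

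The cost is two text changes and one further model run on data already collected. The downside is that the reduced score leaves out genuine activity gains, so it can support the primary analysis but not replace it.
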